### Baseline obstetric characteristics of first 500 randomised patients

Baseline obstetric characteristics of the first 500 enrolled patients in the study are shown in table 3.

**Table 3 T3:** Baseline obstetric characteristics of the first 500 randomised patients in clinical trial. All values are absolute numbers (%) or mean (SD).

	CTG group	CTG + ST group
	
	**n **= 254	**n **= 246
**Age at delivery **(yrs)	32 ± 5	32 ± 5
**Nulliparous**	120 (47.2%)	130 (52.8%)
**Previous ceasarean section**	45 (17.7%)	30 (12.2%)
**Gestational age at delivery (wks)**	40 ± 1.5	40 ± 1.5
**Prolonged pregnancy **(> 42 gestational wks)	31 (12.2%)	24 (9.8%)
**Induction of labour**	82 (32.3%)	87 (35.4%)
**Epidural analgesia**	79 (31.1%)	73 (29.7%)
**Meconium-stained amniotic fluid**	62 (24.4%)	61 (24.8%)
**Oxytocin augmentation**	146 (57.5%)	156 (63.4%)
**Birthweight (gr)**	3506 ± 528.7	3501 ± 508.1

### Ethical considerations and Safety Committee

The study protocol has been approved by the Medical Ethical Committee of the University Medical Center Utrecht, Utrecht, The Netherlands (05/157-K). Written informed consent will be obtained from each participating patient.

Serious Adverse Events (SAE) are defined as "metabolic acidosis (arterial pH < 7.00 and BD_ecf _>12 mmol/L) and admission to a Neonatal Intensive Care Unit (NICU)" or "an Apgar score < 7 after 5 minutes and admission to a NICU". Given the conflicting results in the literature, all SAE's will be reported to the Data Safety Monitoring Committee, consisting of an independent gynaecologist, neonatologist, epidemiologist and a biostatistician. This committee will consider the reported incidence of SAE's at regular intervals to determine whether there are significantly more serious adverse events in the STAN-group and, if so, whether the study should be discontinued. For this purpose the computer program PEST, version 4, will be used [32].

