## Background

The aim of intrapartum fetal monitoring is to identify fetuses at risk for neonatal and long-term injury due to asphyxia. Although cardiotocography (CTG) is applied on a large scale, this technique is still subject to debate [1-3]. Long-term follow-up studies on intrapartum fetal heart rate monitoring have shown no or little benefit on neonatal outcome and a significant increase in operative deliveries [4-6]. Fetal blood sampling (FBS) can be used in addition to CTG, but requires expertise, is invasive, has to be repeated when CTG abnormalities persist and may cause complications [7,8]. As a consequence, it is not widely applied [9]. In The Netherlands, FBS is available in only 50 % to 70 % of the hospitals.

Because changes in the ST-segment of the electrocardiogram (ECG) are related to metabolic acidosis of the fetus, detection of changes in this part of the fetal ECG, in combination with CTG, is a non-invasive and promising alternative for FBS [10,11]. A recent study in more than 600 women showed that ST-changes were present in all cases with severe metabolic acidosis and that CTG plus ST-analysis was more specific in detecting fetal acidemia than CTG alone [12].

Two large randomised trials comparing CTG and ST-analysis of the fetal ECG showed a decrease in metabolic acidosis and interventions for fetal distress in favour of the CTG plus ECG-group [13,14]. The rate of infants with encephalopathy was also significantly lower in the CTG plus ECG-group [15]. However, in both trials FBS was still frequently performed in both arms. Hence, it remains difficult to conclude if the observed improved outcome was indeed due to management to address metabolic acidosis based on ST-analysis results or on FBS results.

Just before the initiation of the present study a third and much smaller randomised trial on ST-analysis versus conventional CTG appeared. This study showed, although not significant, an opposite effect on the incidence of neonatal acidemia or metabolic acidosis, compared to previous trials [16]. The caesarean section and vacuum outlet rate was comparable in both groups. The only significant difference was the incidence of FBS, which was much lower in the ST-analysis group (7.0%) than in the CTG group (15.6%). The results of this trial further stress the need for subsequent research.

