### Outcome measures

#### Primary outcome measures

The primary outcome will be the incidence of serious metabolic acidosis defined as a pH < 7.05 and a BD_ecf _> 12 mmol/l in the umbilical cord artery [26].

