#### Secondary outcome measures

Secondary outcomes are:

1. Instrumental delivery rate because of fetal distress, failure to progress or a combination of the two

2. Neonatal outcome defined as Apgar scores < 4 after 1 minute and/or < 7 after 5 minutes

3. Need for admission to neonatal medium or intensive care unit

4. Incidence of performance of FBS in both groups

5. Cost-effectiveness of both monitoring strategies in general and across hospitals.

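### Both serious adverse event definitions behind the stopping review require NICU admission, so a death without NICU admission does not enter the harm comparison

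*Protocol article*

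**What the plan says.** The Protocol article, section Ethical considerations and Safety Committee, gives the SAE definition in full, as two alternatives. The first is "metabolic acidosis (arterial pH < 7.00 and BD_ecf _>12 mmol/L) and admission to a Neonatal Intensive Care Unit (NICU"), the second "an Apgar score < 7 after 5 minutes and admission to a NICU". There is no third alternative.

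The same section makes these events the basis for stopping: "This committee will consider the reported incidence of SAE's at regular intervals to determine whether there are significantly more serious adverse events in the STAN-group". If there are, the committee considers whether to discontinue. PEST version 4 is named as the tool.

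Three other sections draw the lines differently:

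- Primary outcome measures: "The primary outcome will be the incidence of serious metabolic acidosis defined as a pH < 7.05", with a base deficit above 12 mmol/l and no admission condition.
- Secondary outcome measures: "Need for admission to neonatal medium or intensive care unit".
- Follow up: children admitted to neonatal intensive care or high care for birth asphyxia or delivery trauma are checked at 6 months.

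Death and stillbirth are named neither in the SAE definition, nor in the monitoring text, nor among the outcomes.

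**The concern.** In a trial of fetal surveillance during labour, the gravest failure is a baby who dies before or shortly after birth. Such a baby may never reach a NICU. If NICU admission is a condition of every SAE, that death is a non-event in the one harm comparison the article describes.

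The NICU condition also makes the count depend on where a sick newborn is cared for. The trial runs in nine hospitals, academic and non-academic (Setting), and admission practice may differ between them. Stratifying randomisation by centre protects the balance between arms, but it does not recover events that were never counted.

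Finally, the article justifies reporting SAEs to the committee by conflicting results in the literature. The Background describes that conflict as "an opposite effect on the incidence of neonatal acidemia or metabolic acidosis, compared to previous trials", and Sample size gives relative risks of 0.5, 0.4 and 2.4. Acidosis at the trial's own primary threshold is nevertheless not the quantity in the stopping review. All this concerns a trial in which fetal blood sampling is deliberately restricted in the ST-analysis arm.

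**Working it through.** **Step 1: apply the stated definitions to the possible cases.** The acidosis alternative (A) needs pH < 7.00, BDecf > 12 and NICU. The Apgar alternative (B) needs a 5-minute Apgar < 7 and NICU.

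| Case | A | B | In stopping count | Primary outcome |
|---|---|---|---|---|
| Intrapartum or labour-ward death, no NICU admission | no | no | no | only if cord values qualify |
| pH < 7.00, BDecf > 12, medium or high care only | no | no | no | yes |
| 5-minute Apgar < 7, medium or high care only | no | no | no | depends on cord values |
| pH 7.00 to < 7.05, BDecf > 12, NICU, 5-minute Apgar ≥ 7 | no | no | no | yes |
| pH 7.00 to < 7.05, BDecf > 12, NICU, 5-minute Apgar < 7 | no | yes | yes | yes |
| pH < 7.00, BDecf > 12, NICU | yes | depends on Apgar | yes | yes |
| Death after NICU admission, A or B met | at least one | at least one | yes | depends on cord values |

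The first four rows are the gap. Row five shows that the pH difference alone does not exclude a primary event.

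**Step 2: reproduce the plan's sample size, which fixes the number of primary events.** Inputs (Sample size): 3.5% and 2.1%, two-sided alpha 0.05, power 0.80.

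- Uncorrected: n = [1.96·√(2·0.028·0.972) + 0.8416·√(0.035·0.965 + 0.021·0.979)]² / 0.014² = 2179 per arm.
- With continuity correction: (n/4)·[1 + √(1 + 4/(n·0.014))]² = 2320 per arm, 4640 in total.

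The article states 2319 per arm and 4638 in total, so the figure reproduces with the correction.

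Expected primary events: 2319 × 0.035 = 81.2 (control) and 2319 × 0.021 = 48.7 (ST-analysis), 129.9 in total.

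**Step 3: how many of these are SAEs?** The article gives no pH distribution, NICU admission rate or expected SAE rate. Let f be the share of primary events that meet A or B (an assumption). The counted events are 130 × f:

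- f = 0.1: 13
- f = 0.3: 39
- f = 0.5: 65
- f = 0.7: 91
- f = 0.9: 117

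**Step 4: what f would mean for detecting harm.** As an illustration, take a control SAE rate p₁ = 0.035·f, an ST-analysis rate p₂ = RR·p₁, the same f in both arms, 2319 per arm, and one two-sided 0.05 test at full size. Power is Φ{(p₂ − p₁ − 1.96·SE₀)/SE₁}, where SE₀ is the pooled and SE₁ the unpooled standard error.

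| f | Power, RR 2.0 | Power, RR 2.4 |
|---|---|---|
| 0.1 | 38% | 58% |
| 0.2 | 65% | 87% |
| 0.3 | 82% | 97% |
| 0.5 | 96% | 99.8% |

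This ignores SAEs that are not primary events. It is not the PEST sequential design, whose settings the article does not give; early looks would have less power.

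**Step 5: deaths.** The article gives no expected number. Deaths without NICU admission contribute zero to the comparison whatever their split by arm, so their effect on it cannot be quantified from the document.

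**The case against.** The strongest case on the other side has four parts.

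- **A safety event may be stricter than the efficacy endpoint.** Nothing requires the two pH limits to match. This stands: the pH difference needs an explanation, not necessarily a change.
- **Not every death is lost.** A baby who dies after NICU admission and meets either alternative is counted. This also stands, and it confines the gap to deaths without NICU admission.
- **The article is condensed.** It does not say that the committee sees nothing but these SAEs, and a full protocol or charter may provide for reporting deaths. This stands in part. A reader might infer that deaths go unreported altogether; the article does not say so. But it states a closed SAE definition and ties the stopping comparison to it, so condensation does not remove the gap in the stated text.
- **Giving the committee the primary outcome by arm at each look is a trade-off.** No interim analysis of that endpoint is described, and its status would have to be settled. This stands, so it is not part of the fix.

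Two stronger readings are tempting. One is that most primary-outcome events escape the count. That is true only if f is below 0.5, and f cannot be derived; the Apgar alternative also recovers some events with pH 7.00 to below 7.05. The other is that a real excess would pass unseen at every look. Step 4 does not show that: at a relative risk of 2.4, the value for the third trial, power at full size is 87% or more once f reaches 0.2.

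**Conclusion.** The point holds for deaths on the stated text alone, with no numerical assumption: a death before or without NICU admission meets neither SAE alternative and is absent from the comparison that decides on stopping. It also holds that severely acidotic or low-Apgar babies outside a NICU are not counted, although the article treats high care and medium care admission as relevant elsewhere.

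Some of the roughly 130 planned primary events are not counted either. The share is not stated, and the power figures rest on an assumed f and a single test. They show only that the loss could matter if f is small. The omission of deaths needs correcting; the NICU-only condition and the pH difference need to be reconciled or explained.

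**What to change.** 1. Amend the SAE definition so that any intrapartum or neonatal death counts irrespective of admission, and include these deaths in the PEST comparison.
2. Report perinatal deaths by arm in the final results.
3. Reconcile the NICU-only condition with the wider admission categories in Follow up and Secondary outcome measures, and the SAE pH limit with that in Primary outcome measures, or state why they differ. No particular limit is proposed here.

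Cost: one amendment and a few more reports to the committee. Cord gases, Apgar scores and admissions are already needed for the stated outcomes. The article does not say that deaths are recorded, so a data item may have to be added.

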### Concluding remarks

This study is the first randomised trial to quantify the cost-effectiveness of ST-analysis of the fetal ECG during labour and the first to achieve data about the use of ST-analysis with fetal blood sampling performed only in well-defined circumstances. This study aims to provide additional evidence on the true clinical value of intrapartum ST-analysis and also the clinical indications in which fetal blood sampling still might be necessary in addition to ST-analysis.

## Abbreviations

CTG – cardiotocogram

ECG – electrocardiogram

FBS – fetal blood sampling

STAN – ST ANalysis

NICU – neonatal intensive care unit
